**Probable**
The following attributes will be applicable to the adverse events in question that are deemed, following a meticulous medical assessment, to be linked to the surgical procedure (S-MVi or TMVi) with a high degree of reliability. There is a clear temporal relationship between the event and the surgical procedure. The event is a representative example of the typical postoperative course, which can be ascribed to a commonly observed underlying condition among the general population or individual. The incident in question is not a documented outcome of the surgical intervention in question, and there is no reasonable basis for attributing it to an alternative cause

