In alignment with the directives set forth by the FDA, an adverse event is classified as serious when it results in death, is life-threatening, causes significant or prolonged disability, requires protracted hospitalization, gives rise to a birth defect or congenital abnormality, or, at the discretion of the investigative team, presents other notable hazards or potential for serious injury to the study enrollees or other individuals. In the opinion of the attending clinician, it may be considered appropriate to categorize an episode that is neither lethal nor life-threatening and does not necessitate hospitalization as a serious adverse event. This is on the grounds that a reasonable medical judgment may exist that such an episode may endanger the patient and necessitate medical or surgical intervention in order to avert one or more of the potential outcomes listed in the definition. The subsequent list provides exemplars of medical episodes that may require medical or surgical attention. Such conditions include bronchospasm necessitating intensive treatment in an emergency department or at home, blood dyscrasias, and convulsions that do not result in the need for in-patient hospitalization.

○Unexpected major adverse events.

An unanticipated major adverse incident is defined as a critical adverse occurrence that does not fall within the parameters set forth in the established clinical trial protocol or is not duly recorded in the documentation provided to the patient for review and signature. In the event of an unexpected serious adverse event, it is mandatory to provide unscheduled notification.

In the course of the follow-up period, the occurrence of any adverse events will be duly recorded. The onus will be incumbent upon the investigating physician to ascertain whether a causal relationship exists between the adverse incident in query and the intervention that has been undertaken. The concept of causality is elucidated in Table 5.

▪Specific Adverse Event Definitions.

A myocardial infarction (MI) is defined as a clinical syndrome characterized by the presence of at least one of the following diagnostic criteria, which collectively indicate myocardial necrosis and are consistent with myocardial ischemia [38]. These criteria include the following:Myocardial infarction.

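### The *Probable* row of Table 5 contradicts its stated purpose and itself, so a recognised complication of surgery or TEER has no proper causality category

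*Protocol article*

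**What the plan says.** Section 2.3 of the protocol article, under unexpected major adverse events, assigns the causality judgement: "The onus will be incumbent upon the investigating physician to ascertain whether a causal relationship exists" between the event and the intervention. It then points to the definition: "The concept of causality is elucidated in Table 5".

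Table 5 has three grades. *Probable* is for events judged, after medical assessment, "to be linked to the surgical procedure (S-MVi or TMVi) with a high degree of reliability". The row introduces its content with "The following attributes will be applicable to the adverse events in question" and then lists:

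- timing: "There is a clear temporal relationship between the event and the surgical procedure";
- typicality and origin: "The event is a representative example of the typical postoperative course, which can be ascribed to a commonly observed underlying condition", in the general population or the individual;
- documentation: "The incident in question is not a documented outcome of the surgical intervention in question";
- alternatives: no reasonable ground for assigning the event to another cause.

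*Possible* covers events that fall short of *Probable* without a firm conclusion. Its attributes are that the event follows the procedure and can be attributed neither to the surgery nor to known related conditions. *Unlikely* covers events for which a causal link is implausible. Its attributes are a time course that does not match the procedure, no recognisable response pattern, and a plausible environmental cause.

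**The concern.** A causality scale should give its top grade to events that follow the procedure closely, are known or plausible consequences of it, and have no better explanation. The *Probable* row reverses the second of these by asking that the event not be a documented outcome. It also blurs the third by letting the event be ascribed to an underlying condition. The documentation attribute looks as if it belongs to expectedness, which section 2.3 already treats separately under unexpected major adverse events.

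This is a stated rule that is wrong as written, not a detail left to a fuller document. The row is complete and grammatical, and nothing elsewhere in the article corrects it. At stake is whether relatedness is rated correctly, and in the same way at every center, in a study that compares the safety of two quite different procedures.

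**Working it through.** No arithmetic applies. The check sets the attributes of Table 5 side by side.

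**Step 1. Do the *Probable* attributes agree with one another?**

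| One attribute | Set against | Result |
|---|---|---|
| Purpose: reliably linked to the procedure | Not a documented outcome of it | Works against the purpose: the best-established links are the ones ruled out |
| Typical of the postoperative course | Not a documented outcome of the procedure | Conflict: what is typical after a procedure is normally documented for it |
| Ascribable to a common underlying condition | No reasonable alternative cause | Conflict: the underlying condition is an alternative cause |

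**Step 2. Where does a recognised complication go?** Take a test event that is close in time to the procedure, recognised as a complication of it, and without another explanation. The protocol's own specific adverse event definitions supply candidates: wound dehiscence, failure to come off the ventilator within 48 h of surgery, and reoperation for hemorrhage or tamponade.

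| Grade | Attribute that decides | Does the test event meet it? |
|---|---|---|
| *Probable* | Not a documented outcome of the procedure | No, it is a recognised one |
| *Possible* | Cannot be attributed to the surgery | No, the surgery is the evident cause |
| *Unlikely* | Time course does not match the procedure | No, it is close in time |

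On the literal wording, the clearest kind of procedure-related event fits the attributes of none of the three grades.

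**Step 3. Which planned results depend on the grade?** In section 2.3, an adverse event counts whether or not it is related to the intervention. The planned safety outputs are frequencies, rates per patient per year, timing, numbers of patients per event category, and incidences with 95% confidence intervals. None is restricted to related events. The primary endpoint (LVEDVI at 10 years), all-cause mortality and MACE do not refer to Table 5.

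**The case against.** The strongest reply is that the row is clumsy rather than unworkable. Entry to *Probable* is a clinical judgement, and the listed attributes describe such events; the row never says that all of them must hold. Typicality of the postoperative course points towards known complications, so a sensible rater would grade them *Probable* anyway. No planned output is conditioned on relatedness, so no reported comparison would change.

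Much of this stands, and it rules out some stronger conclusions that a reader might draw:

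- **That *Probable* is empty, or that no known complication could ever receive it.** This requires the attributes to be jointly necessary. That is the natural reading, since no alternative is offered, but the text does not say so.
- **That related events would slide into *Possible* or *Unlikely*.** The opening of *Possible* works as a residual class, so a rater might use it. The attributes of both lower rows nevertheless exclude a recognised complication, so a systematic downgrading does not follow.
- **That procedural harm would be reported as absent in both arms.** The serious-event outputs do not depend on relatedness, and the article describes no tabulation of related events.
- **That recorded events need re-rating.** The article describes the rating in the future tense and shows no ratings made so far.

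What the reply does not remove is the contradiction. If one rater follows the clause on documented outcomes and another follows the row's purpose, the same event receives different grades, and the protocol gives no way to say which is correct.

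**Conclusion.** The concern holds in a limited form. The *Probable* row conflicts with its stated purpose and contains two internal conflicts. On a literal reading, a recognised complication that is close in time and has no other cause has no proper grade. Relatedness ratings made with this table would be wrong, or inconsistent across the five centers, depending on how each rater resolves the conflict.

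The size cannot be expressed as a number, because it depends on rater behaviour that the document does not describe. The effect stops at the causality classification. The conclusion assumes that a documented outcome means a recognised complication of the procedure, a term the article does not define, and that raters apply the listed attributes as written. The negation is probably a drafting slip, but it is the current text. A correction is worth making before causality is rated or reported.

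**What to change.** Reword Table 5 as follows.

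- **Probable:** a clear temporal relation to the procedure, an event that is a known or plausible consequence of it, and no more likely alternative cause. Delete the clauses on not being a documented outcome and on being ascribable to an underlying condition.
- **Possible:** replace the attribute that the event cannot be attributed to the surgery with wording that places this grade between the other two, for example a plausible relation in time with another cause about as likely.
- **All three rows:** check that they are ordered and that every event falls into exactly one.

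Keep expectedness under its own definition in section 2.3. If any events have already been graded under the present wording, re-rate them; otherwise nothing further is needed.

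The cost is a change to one table and a note to the five centers, plus re-rating if any grades exist. No new data are required, and no endpoint, sample size or planned analysis changes.

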**Possible**
In the event that an adverse event, following a thorough clinical evaluation, does not align with the parameters of a probable relationship with the surgery, but a definitive conclusion has not been reached, it is essential to consider the following characteristics. The event in question occurs subsequent to the surgical procedure. It is not possible to attribute the adverse event to the surgery, nor can it be explained by the known, medically related conditions that have been previously observed.
**Unlikely**
The following characteristics will be taken into account in the event that, subsequent to a thorough medical evaluation, an adverse event does not meet the criteria for a potential or likely correlation with the surgery in question and a causal link does not appear to be plausible. The chronological progression of events does not align with the sequence of actions undertaken during the surgical procedure. It is not possible to discern a clear pattern of response to the surgical procedure, and it is plausible that the event may have been caused by environmental factors.

**Table 6 jcm-13-07742-t006:** Outline of the criteria for defining postoperative acute kidney injury †. † The serum creatinine level undergoes fluctuations during the course of hospitalization.

Criteria Used to Define Postoperative Acute Kidney Injury †	
Level	Creatinine in Serum
1	An increase of 1.5–1.9 times the baseline, or an increase of at least 0.3 mg/dL (26.5 micromol/L), is to be expected.
2	2 to 2.9 times the baseline.
3	An increase to 3.0 times the baseline is indicated or, alternatively, a value of 4 mg/dL (353.6 micromol/L) should be reached, at which point renal replacement therapy should be initiated.

## Acronyms

AE	adverse event
CABG	coronary artery bypass surgery
CHF	chronic heart failure
COAPT	Cardiovascular Outcomes Assessment of the MitraClip Percutaneous Therapy
GDMT	guideline-directed medical therapy
HF	heart failure
ICU	intensive care unit
LV	left ventricle
LVEDP	left ventricular end-diastolic pressure
LVEF	left ventricular ejection fraction
MACE	major adverse cardiac events
MCG	Medical College of Georgia
MI	myocardial infarction
MV	mitral valve
NYHA	New York Heart Association
PCI	percutaneous coronary intervention
PCWP	pulmonary capillary wedge pressure
RCT	randomized clinical trials
RER	respiratory exchange ratio
RMA	restrictive mitral annuloplasty
RPE	rate of perceived exertion
SV-r	subvalvular repair
SMR	secondary mitral regurgitation
S-MVi	standard mitral valve intervention
TEER	transcatheter edge-to-edge mitral valve repair (TEER)
TEERMISO	Transcatheter Versus Standard Surgical Mitral Valve Operation for Secondary Mitral Regurgitation
TMVi	transcatheter mitral valve intervention
